### 2.13. Statistical Analysis

Statistical analysis will be conducted using Statistica 13.1 (StatSoft, Tulsa, OK, USA). Our intention is to conduct intention-to-treat analyses. Continuous data will be presented as means and standard deviations or as medians and ranges, while categorical variables will be expressed as proportions. Normally distributed continuous variables will undergo analysis using the Student’s *t*-test, while the Wilcoxon rank-sum test will be applied for skewed data. Categorical variables will be analyzed using either the chi-square test or Fisher’s exact test. The 95% confidence intervals (95% CIs) will be calculated for relative risk, as well as risk differences for categorical variables, and mean differences with 95% CIs will be calculated for continuous variables. We plan to analyze the partial data once annually during the recruitment of patients.

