## 2. Materials and Methods

### 2.1. Study Design

We are implementing an unblinded, parallel-group, randomized controlled superiority trial. Parents of neonates born between 24 + 0/7 weeks and 32 + 6/7 weeks of gestation will be offered the opportunity to participate in the study within the first 24 h of the infant’s life. After providing information orally and in writing concerning the study, we will seek written consent from the parents for the neonate and mother to participate in the trial. To enhance the relevance of the research findings, we will stratify the study group by gestational age into 24–28 and 29–32 weeks of gestation subgroups. We have planned to recruit for the study for 36 months, from September 2024 to the end of 2027. The study protocol has been registered at ClinicalTrials.gov (identifier: NCT06199102). Please see Table 1 for all planned patient-related activities.

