### 2.2. Setting and Participants

All infants admitted to the Department of Neonatology and Intensive Care at the Medical University of Warsaw (Warsaw, Poland) and born at 24 + 0/7 weeks to 32 + 6/7 weeks of gestation will be considered for inclusion. Our tertiary perinatal center has an annual number of births of approximately 2500 infants, including an average of 80 infants aged <33 weeks of gestation. 25(OHD) neonatal birth concentration strongly correlates with pregnant vit D supplementation. According to the Polish Society of Gynecologists and Obstetricians, it is recommended to supplement vit D at a dose of 1500–2000 IU/day during pregnancy [19]. However, the available multivitamin supplements for pregnant women in Poland vary from 400 IU to 2000 IU. The parents of the infants will provide informed consent. Patients will be randomly assigned to the monitored group or the controlled group. We will collect a cord or vein blood sample within the first 48 h of life to evaluate 25(OH)D levels at birth. Blood samples will be taken simultaneously with other laboratory tests so as not to expose the newborn to additional blood donations. Additionally, the maternal 25(OH)D level and the neonatal birth levels of PTH and IL-6 will be measured. Once infants reach a daily enteral feeding volume of 30 mL/kg, they will receive an initial vitamin D dose. We will continue to monitor the supplementation until 35 weeks of PCA.

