### 2.5. Randomization Criteria

Following the receipt of signed consent for participation from the parents of the neonates, the participants will be registered and randomized within the initial 48 h. Enrolled infants will be randomized (1:1 allocation) with a block size of six.

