### 2.7. Primary Outcome

The percentage of infants with deficient or suboptimal 25(OH)D levels at 28 ± 2 days of age will be the primary endpoint. The 25(OH)D levels will additionally be measured at 35 ± 1 weeks of PCA. Neonatal staff will obtain venous samples of 0.3 mL to assess the 25(OH)D serum concentration. The study site will utilize the VIDAS automated quantitative test (bioMérieux, Marcy l’Etoile, France) to measure 25(OH)D concentrations. In Poland, the diagnostic thresholds for serum 25(OH)D concentrations are as follows [7]: <20 ng/mL (50 nmol/L) indicates vitamin D deficiency;
>20 ng/mL (50 nmol/L) and <30 ng/mL (75 nmol/L);≥30 ng/mL (75 nmol/L) up to 50 ng/mL (125 nmol/L) reflect adequate to optimal vitamin D status;>50 ng/mL (125 nmol/L) up to 100 ng/mL (250 nmol/L) indicate a high vitamin D supply;>100 ng/mL (250 nmol/L) reflect an increased risk for intoxication [7].

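### The primary analysis is a valid but unadjusted two-group test; adjusting for the birth 25(OH)D already collected would probably gain power at almost no cost

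*Protocol article*

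**What the plan says.** Section 2.7 makes the primary endpoint binary: the percentage of infants with "deficient or suboptimal 25(OH)D levels at 28 ± 2 days of age will be the primary endpoint". With the thresholds listed there, this means a value below 30 ng/mL.

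Section 2.13 assigns tests by type of variable: "Categorical variables will be analyzed using either the chi-square test" or Fisher's exact test. Confidence intervals "will be calculated for relative risk, as well as risk differences for categorical variables". No stratum or baseline term is named.

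Two other parts of the protocol supply information that these tests do not use:

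- Section 2.2: "We will collect a cord or vein blood sample within the first 48 h of life to evaluate 25(OH)D levels at birth". Table 1 schedules the same sample in the first 48 h of life.
- Section 2.1: "we will stratify the study group by gestational age into 24–28 and 29–32 weeks of gestation subgroups".

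Section 2.5 describes the allocation only as follows: "Enrolled infants will be randomized (1:1 allocation) with a block size of six". It mentions no strata.

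**The concern.** Birth 25(OH)D is the same analyte as the endpoint, measured about four weeks earlier, and it is unaffected by allocation. The protocol gives reasons to expect it to vary between infants. The Introduction ties neonatal stores to the mother's level, and section 2.2 notes that prenatal products in Poland range from 400 to 2000 IU. A covariate of this kind is the usual first candidate for adjustment, because the variation in outcome that it explains no longer blurs the treatment comparison.

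There is little power to spare. Section 2.12 requires 54 per group and sets the total at 130 with 20% loss. Losing 20% of 130 leaves 130 × 0.8 = 104, or 52 per arm, slightly below the requirement. A gain from data already being collected would therefore be useful.

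**Working it through.** **Inputs.** From section 2.12: control rate 80%, decrease of 25% (read as percentage points, so 80% vs 55%), power 80%, α = 0.05 (taken as two-sided), 54 per group, 130 in total, 20% loss. The same section gives 45% at day 28 in the department's previous study. A comparison of 45% vs 20% mirrors 55% vs 80%, so two-group power is the same for both. Assumed, because the protocol does not give them: the association of birth 25(OH)D and of stratum with the day-28 outcome, and the relative size of the strata.

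**Step 1: reproduce the plan's figure.** Pooled-variance formula without continuity correction:

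n = [1.960 × √(2 p̄ q̄) + 0.842 × √(p₁q₁ + p₂q₂)]² / d²

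with p̄ = 0.675, 2 p̄ q̄ = 0.43875, p₁q₁ + p₂q₂ = 0.16 + 0.2475 = 0.4075 and d = 0.25:

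n = (1.298 + 0.537)² / 0.0625 ≈ 53.9, so 54.

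The stated size is that of the unadjusted, uncorrected chi-square test. Power by this formula is 80.1% at 54 per arm and 78.5% at 52. Exact calculation gives 80.7% and 79.3%.

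**Step 2: power with adjustment, 52 per arm.** Simulation of 45% vs 20% with a modest stratum effect and an assumed correlation between birth and day-28 25(OH)D. The adjusted test is the likelihood-ratio test for arm in a logistic regression on arm, birth 25(OH)D and stratum. Ranges show the spread between repeated simulations.

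| Assumed correlation | Unadjusted chi-square | Adjusted |
|---|---|---|
| 0 | about 80% | about 80% |
| 0.3 | 79–80% | about 83% (82–84%) |
| 0.5 | 79–80% | 85–87% |
| 0.6 | 79–80% | 88–90% |

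With 4000 trials per setting, the simulation standard error at 80% power is √(0.8 × 0.2 / 4000) = 0.006, or about 0.6 points. Differences of a point or two between runs are noise.

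**Step 3: a second model, 54 per arm.** 80% vs 55%, equal strata, covariate effects set as log-odds (baseline per SD / stratum), 4000 trials per row.

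| Baseline / stratum | Chi-square | Mantel-Haenszel by stratum | Adjusted logistic |
|---|---|---|---|
| 0 / 0 | 80.3% | 80.0% | 80.6% |
| 0.5 / 0.3 | 81.3% | 81.4% | 83.9% |
| 1.0 / 0.5 | 80.4% | 80.5% | 86.8% |
| 1.5 / 0.5 | 79.7% | 79.7% | 91.3% |
| 2.0 / 0.5 | 81.3% | 81.5% | 94.9% |
| 0 / 1.0 | 81.5% | 82.3% | 83.2% |

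The gain comes from the birth value. Stratifying alone moves power by about 1 point or less, even with a stratum log-odds of 1.0.

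**Step 4: type I error.** With 45% in both arms, the adjusted test rejects in 5.1–5.6% of trials and the chi-square in 5.3–6.1%. With 80% in both arms (1.0 / 0.5), the figures are 5.9% and 5.1%. The adjusted test is close to 5%, slightly above it in the second setting.

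**The case against.** The strongest reply is that nothing here is an error. The unadjusted chi-square is valid in a randomised trial, it is the test on which the sample size rests, and its confidence interval already allows for chance imbalance. A journal article may also leave an adjusted model to a separate analysis plan. All of this stands, except that section 2.13 does name its tests and, as written, they are unadjusted. The point is therefore an improvement to a stated method.

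Some stronger readings are not supported:

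- A reader might infer that the plan certainly discards power. The birth-to-day-28 correlation appears nowhere in the protocol, and at zero the gain is nil. There are reasons why it could be modest: supplementation moved the department's rate from 80% at birth to 45% at day 28, the birth sample may be cord or venous blood, and the Discussion concedes epimer cross-reactivity in the assay.
- A reader might infer that ignoring the strata makes the standard errors too wide. Section 2.5 does not say that randomisation is stratified, and section 2.1 can be read as planning subgroups. Even if randomisation is stratified, the effect on power is about 1 point.
- A reader might count the open choice between chi-square and Fisher as a separate defect, since Fisher has 74.7% power at 54 per arm. At 52 per arm and 45% vs 20%, the smallest expected count is about 52 × 0.325 = 16.9, far above the usual threshold of 5, so Fisher would ordinarily not be used for this endpoint. The wording also serves rarer outcomes.

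The gain depends somewhat on the test used. With a Wald test at 52 per arm it is smaller: 79.5% to 80.9% at correlation 0.3, and 80.3% to 85.0% at 0.5. A test based on the standardised risk difference gave 84%, 86% and 90% at 0.3, 0.5 and 0.6, much like the likelihood-ratio test.

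**Conclusion.** The point holds as a conditional efficiency gain. The planned test is valid and matches the sample-size basis, but it leaves unused a baseline measurement of the endpoint's own analyte. If birth 25(OH)D is prognostic, adjustment raises power at 52 per arm from about 79–80% to about 83% at correlation 0.3, 85–87% at 0.5 and 88–90% at 0.6, with type I error near 5%. If it is not prognostic, adjustment costs essentially nothing. These figures rest on assumed correlations, a modest assumed stratum effect, and the protocol's 25-point difference. The case for the stratum term is consistency with the groups named in section 2.1, since it adds little power.

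**What to change.** In section 2.13, prespecify one primary analysis: logistic regression of 25(OH)D below 30 ng/mL at day 28 on arm, gestational-age stratum (24–28 vs 29–32 weeks) and birth 25(OH)D as a continuous variable. From this model report the standardised (marginal) risk difference and relative risk with 95% CIs, which keeps the effect measures already promised. Name in advance the test that supplies the p value: the likelihood-ratio test or the test of the standardised risk difference. Keep the uncorrected chi-square, the test behind 54 per group, as the sensitivity analysis.

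Add a simple rule for missing birth samples so that no randomised infant drops out of the model for that reason, for example substituting the mean birth value over both arms combined. In section 2.5, state whether randomisation is stratified by the same two groups.

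The cost is wording, slightly more analysis work and the missing-sample rule. No extra infants, samples or visits are needed.

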### 2.11. Data Monitoring

We opted not to establish a data monitoring committee since the intervention in the trial (i.e., vit D supplementation of 250–1000 IU/day) aligns with the standard of care supported by multiple pediatric societies [7,13,14]. Moreover, we are well-informed about the potential adverse effects associated with this intervention.

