### 2.12. Sample Size Calculations

The sample size was determined based on the primary outcome, which is defined as the count of neonates with 25(OH)D deficiency or insufficiency. A previous study conducted in our department reported an incidence of vit D deficiency or vit D insufficiency of 80% in preterm infants at birth, which was reduced with vit D supplementation to 45% at 28 ± 2 days of age. Assuming an estimated prevalence of 80% in the standard supplementation group, we chose to detect a decrease of 25% in patients with vitamin D deficiency and vitamin D insufficiency versus the control group with a power of 80% and α = 0.05 to meet acceptable recruitment rates and reach statistically significant results. Hence, 54 infants are required in each study group. Assuming a 20% loss to follow-up (due to the decision of the principal investigator, withdrawal of consent from a parent/legal guardian), the sample size has been set at 130 patients and their mothers. We believe the recruitment of patients will last approximately 3 years.

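### Yearly analyses of partial data are planned without a stated purpose, boundary or access limit; if they test the arms at 0.05 and can be acted on, type I error exceeds 5%

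*Protocol article*

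**What the plan says.** Section 2.13 of the protocol article names the between-group methods: t-test or Wilcoxon for continuous data, chi-square or Fisher's exact test for categorical data, and 95% confidence intervals for relative risks and differences. Its last sentence is "We plan to analyze the partial data once annually during the recruitment of patients". Nothing more is said about these analyses.

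Three other sections set the context:

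- **Design (2.1):** "We are implementing an unblinded, parallel-group, randomized controlled superiority trial".
- **Monitoring (2.11):** "We opted not to establish a data monitoring committee since the intervention in the trial", followed by the reason that the dose range agrees with accepted practice.
- **Sample size (2.12):** one comparison, "with a power of 80% and α = 0.05 to meet acceptable recruitment rates".

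The length of recruitment fixes the number of annual looks, and it is given in two ways. Section 2.12 says "We believe the recruitment of patients will last approximately 3 years". Section 2.1 says "We have planned to recruit for the study for 36 months, from September 2024 to the end of 2027"; September 2024 to December 2027 is 40 calendar months.

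**The concern.** The article commits to examining accumulating data every year and leaves open what is examined. The only methods described are ordinary single-look tests with 95% intervals, and the commitment follows directly after them. A study team could therefore reasonably follow the section by running those tests by arm each year.

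Two things are then at stake:

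- **Error rate.** Testing the same endpoint repeatedly at 0.05, with any significant result allowed to count, gives a false-positive rate above the 5% on which the sample size rests.
- **Conduct.** Without a committee or a stated access limit, nothing in the text keeps comparative results from the people who recruit and treat. That could affect enrolment, the decision to continue, and the threshold for suspecting sepsis, which section 2.8.1 bases partly on clinical signs. The primary endpoint is a laboratory threshold and is less exposed.

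Timing matters too, because a boundary chosen after arm-level results have been seen cannot restore error control.

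**Working it through.** **Step 1. Reproduce the sample size.** Inputs from section 2.12: control rate 80% ("Assuming an estimated prevalence of 80% in the standard supplementation group"); a difference of 25 percentage points ("we chose to detect a decrease of 25% in patients with vitamin D deficiency and vitamin D insufficiency versus the control group"), so 55% in the monitored arm; power 80%; α = 0.05. The article does not state one- or two-sided. With pooled variance under the null and no continuity correction:

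n per arm = [z(0.975) × √(2 × p̄ × (1 − p̄)) + z(0.80) × √(p1(1 − p1) + p2(1 − p2))]² / (p1 − p2)²

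- p̄ = (0.80 + 0.55)/2 = 0.675, so √(2 × 0.675 × 0.325) = 0.6624
- √(0.16 + 0.2475) = 0.6384
- n = (1.960 × 0.6624 + 0.8416 × 0.6384)² / 0.0625 = 53.9, rounded up to 54

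This matches the stated 54 per group (a one-sided test would give 43). The number is that of a fixed design at two-sided 0.05. It does not prove that no boundary exists, because an O'Brien-Fleming design with three looks would need at most 56 per arm.

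**Step 2. Count the looks.** The number is an assumption, because the article does not give it.

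- Three years of recruitment: analyses after years 1 and 2 plus the final, three looks.
- 40 months: analyses at months 12, 24 and 36 plus the final, four looks. With even accrual the information fractions are 12/40, 24/40 and 36/40, that is 0.30, 0.60 and 0.90, then 1.
- Faster accrual: section 2.2 gives about 80 eligible births a year, so 130 infants could at the earliest be reached in 130/80 = 1.6 years. That gives one annual analysis plus the final, two looks.

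**Step 3. Overall type I error if every look is tested at two-sided 0.05.** Under the null the test statistics are jointly normal with corr(Zi, Zj) = √(ti/tj) for ti < tj. The quantity is the probability that |Z| > 1.96 at one or more looks.

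| Looks including final | Information fractions | Overall error |
|---|---|---|
| 1 | 1 | 5.0% |
| 2 | 1/2, 1 | 8.3% |
| 3 | 1/3, 2/3, 1 | 10.7% |
| 4 | 0.30, 0.60, 0.90, 1 | 11.8% |
| 4 | 1/4, 1/2, 3/4, 1 | 12.6% |

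**Step 4. Check with the binary endpoint and the named tests.** Simulation with looks at 18, 36 and 54 infants per arm and common rates from 45% to 80%:

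- chi-square at every look: 10.6% to 11.3%
- chi-square, with Fisher's test when an expected count is below 5: 9.0% to 11.2%
- Fisher's test at every look: 5.5% to 6.1%. Its single-look error in these settings is only 2.6% to 3.1%, so it also about doubles, but from a lower start. With four looks it is 5.9% to 7.0%.

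**Step 5. Check the remedy.** With p < 0.001 required at each interim look (|Z| > 3.29) and 0.05 at the end, the same calculation gives 5.0% for two looks and 5.1% for three or four equally spaced looks.

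**The case against.** A reader might infer that the plan as written doubles the false-positive rate. The documents do not support that as a statement of fact. The sentence in section 2.13 does not say that the annual analysis compares the arms, covers the primary endpoint, tests at 0.05, or can end the trial or establish its result. The tests stand in the same paragraph but are not tied to the annual analysis, and no efficacy stopping rule appears anywhere. If the looks are pooled, descriptive or safety-only, or if the conclusion rests on the final test alone, the formal error stays at 5%. This objection stands in full, so the figures are conditional.

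The article is also a condensed text, and a boundary could sit in an analysis plan that is not shown. That too is fair, and the sample size cannot rule it out. What remains is that the article makes a positive commitment to repeated analyses, declines the body that would usually hold the results, and fixes neither purpose nor access.

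The size depends on choices the article leaves open. Fisher's test throughout would leave the error near 6%, and the number and spacing of looks are assumed. Hence a range.

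On conduct, staff already know allocation, and doses in the monitored arm follow individual 25(OH)D results. The lack of blinding by itself can influence suspicion of sepsis, and the extra effect of seeing yearly summaries cannot be quantified from the documents. Nor do they say who would receive those summaries.

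Last, restricting safety review to pooled data would have a cost where there is no committee, since section 2.9 identifies nephrocalcinosis as a known risk. The fix below therefore allows safety data to be reviewed by arm.

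**Conclusion.** The point holds in conditional form. A yearly analysis of partial data is planned in an unblinded trial without a monitoring committee, sized as a fixed design, and its purpose, boundary and audience are not stated.

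The error figures rest on three assumptions: each look compares the arms on the primary endpoint at two-sided 0.05; a significant result at any look can be declared or acted on; and there are two to four looks including the final. Under these, overall type I error is about 8% to 13% with the chi-square test, with 10.7% for the three looks that a three-year recruitment implies. With Fisher's test at each of three looks it is about 5.5% to 6.1%. If the first or second assumption fails, no alpha is spent and only the question of who sees arm-level results remains. An outright claim that the plan doubles the error rate goes further than the text.

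**What to change.** Replace the last sentence of section 2.13 before the first annual analysis takes place. State that the yearly review covers recruitment, data completeness and safety only, and that no between-arm efficacy comparison is made before the final analysis. Safety data may be reviewed by arm, preferably by someone who does not recruit.

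If a between-arm efficacy look is wanted, pre-specify it with a Haybittle-Peto boundary: two-sided p < 0.001 on the primary endpoint at each annual look, final test at 0.05, and results withheld from recruiting staff. If a boundary already exists in an analysis plan, a cross-reference and a statement of who has access would be enough.

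The cost is one paragraph. No infants are added, and power is essentially unchanged because the final test stays at 0.05. The downside is that the investigators give up yearly efficacy results by arm.

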## 3. Discussion

This study aims to evaluate the effectiveness of monitored vit D supplementation in a population of preterm infants and determine whether appropriate vit D supplementation can reduce the incidence of neonatal sepsis and MBD. A meta-analysis published in 2022 on pediatric enteral vit D supplementation reported improved growth and vit D status in preterm and low-birth-weight infants [34]. However, the benefits of a higher dose of supplementation were not found in serious neonatal morbidities except by very low-to-low certainty evidence of a reduction in serum PTH and vit D levels in high-dose vit D supplemented groups. The meta-analysis included 14 trials comprising high versus low supplementation; however, the levels of heterogeneity and risk of bias were high. There is no consensus on the optimal dosage of vit D supplementation for preterm infants. A crucial factor to note is that preterm infants, in particular, are highly vulnerable to the adverse effects of vit D deficiency, given that 80% of the transfer of calcium and phosphorus from the placenta occurs between 24 weeks and 40 weeks of gestation [7,8,9].

There is also controversy regarding the methodology for measuring vit D. Miller et al. suggest that neonatal 25(OH)D measurements alone should not be used for assessing nutritional status due to the unreliability of the method for measuring 25(OH)D in preterm infants. In their opinion, clinical correlation and other laboratory parameters, including ionized calcium, should be considered [35]. In our study, we have chosen to use an immunoenzymatic method with the biological potential limitations of an overestimation of vit D status due to cross-reactivity to epimer. Also, the upper limit of 25(OH)D concentration in preterm infants is controversial. However, to assess vit D toxicity, we will measure serum and urine calcium levels, to prevent nephrocalcinosis, according to Malone et al. [33]. Currently, there is limited research on the immunological regulatory mechanism of vit D in the context of neonatal sepsis.

